## Abstract

**Background:**

Episodes of ischaemia-hypoxia in the perinatal period as well as the changes in the redistribution of blood may lead to decreased perfusion and ischaemia of the cardiac muscle. Additionally, there is a negative impact from the reduced contractility of the cardiac muscle secondary to acidosis and hypoxia. Therapeutic hypothermia (TH) improves the late effects in moderate and severe cases of hypoxia-ischaemia encephalopathy (HIE). The direct impact of TH on the cardiovascular system includes moderate bradycardia, increased pulmonary vascular resistance (PVR), inferior filling of the left ventricle (LV) and LV stroke volume. The above-mentioned consequences of TH and episodes of HI in the perinatal period are therefore exacerbation of respiratory and circulatory failure. The impact of the warming phase on the cardiovascular system is not well researched and currently few data has been published on this topic. Physiologically, warming increases heart rate, improves cardiac output and increases systemic pressure. The effect of TH and the warming phase on the cardiovascular values has a decisive impact on the metabolism of drugs, including vasopressors/inotropics, which in turn affects the choice of medication and fluid therapy.

**Method:**

The study is a multi-centre, prospective, case-control, observational study. The study will include 100 neonates (50 subjects and 50 controls). Echocardiography and cerebral and abdominal ultrasound will be performed in the first 1/2 days after birth as well as during warming i.e., on day 4/7 of life. In neonatal controls these examinations will be performed for indications other than hypothermia, most frequently because of poor adaptation.

**Ethics and dissemination:**

The Ethics Committee of the Medical University of Warsaw approved the study protocol prior to recruitment (KB 55/2021). Informed consent will be obtained from the carers of the neonates at the time of enrolment. Consent for participation in the study can be withdrawn at any time, without consequences and without obligation to justify the decision. All data will be stored in a secure, password-protected Excel file that is only accessible to researchers involved in the study. Findings will be published in a peer-reviewed journal and disseminated at relevant national and international conferences.

**Clinical Trial Registration:**

NCT05574855.

## Introduction

1.

Perinatal hypoxia in the form of HIE is a frequent cause of cerebral impairment in neonates. HIE occurs in 3–5 of 1,000 neonates in developed countries (1) and is significantly higher in developing countries at 25 of 1,000 neonates (2). Despite developments in medicine, increasing understanding of HIE pathophysiology and progress in neonatal intensive care as well as treatment of moderate or severe perinatal asphyxia, HIE continues to be associated with significant mortality and late neurological sequelae (1).

### Impact of hypoxia on the cardiovascular system

1.1.

Transitory hypoxia of the myocardium (and its resultant dysfunction), which may, but not necessarily, present clinically, occurs in two thirds of neonates born with perinatal asphyxia (1). There is no doubt that that this is one of the more frequent cause of circulatory insufficiency. Both an episode of ischaemic hypoxia in the perinatal period and the changes in the distribution of blood may lead to diminished perfusion of the cardiac muscle. An additional but no less important impact on cardiac function is the immaturity of the neonatal myocardium and its reduced contractility secondary to acidosis and hypoxia. Ischaemia and acidosis lead to imbalance in favour of production of endothelin 1, which leads to reduced production of nitric oxide and vasoconstriction of pulmonary vessels and therefore greater PVR which has a detrimental effect on the already impaired right ventricular (RV) function. The weak RV function and increase PVR impair filling and function of the LV and thus, they can affect systemic and cerebral blood flow (2, 3).

### The impact of therapeutic hypothermia on the cardiovascular system

1.2.

TH improves the distant results in cases of moderate and severe HIE and is currently the standard of care for neonates born at or near term (>35 weeks of gestation). The direct effect of TH on the cardiovascular system includes the following:
•Moderate bradycardia resulting from the decreased effect of the parasympathetic system on cardiac function. Indeed, sinus bradycardia leads to reduced stroke volume and decreased requirement for energy by the myocardium (3–5). In turn, administration of inotropes increase metabolic requirements.•Additionally, TH leads to increased PVR, potentially resulting in a clinical picture of persistent pulmonary hypertension in the neonate (PPHN) or its exacerbation in cases of pre-existing raised PVR (3, 6). In animal studies (7), TH was associated with increased PVR, while an increased risk of PPHN with TH was not found in randomized controlled clinical trials (RCTs) (5, 10).•The resulting RV dysfunction and reduced stroke capacity of the RV leads to reduced pulmonary venous return and therefore inferior filling and stroke volume of the LV. A consequence of the effects of TH mentioned above and of an episode of HI in the perinatal period is therefore exacerbation of respiratory and circulatory failure.

### Impact of the warming process on the cardiovascular system following administration of hypothermia

1.3.

The impact of the warming phase on the cardiovascular system has not been well documented and currently very little data was published on this topic. Physiologically warming accelerates the heartbeat and improves stroke volume (6), although the mean blood pressure may fall (7) or remain unchanged as a result of lowering of the diastolic component, which in turn affects metabolism and drug clearance, including clearance of cardiovascular medications. The warming phase, following conclusion of hypothermic treatment, affects the selection of further medicinal therapy in terms of vasopressors, inotropes and of fluid therapy. Furthermore, studies have shown that neonates are more at risk of convulsive episodes during the warming phase. In a study of 160 neonates, 9% experienced intra- or periventricular haemorrhage. Neonates require more precise observation in terms of haemodynamic instability during the warming phase (5) (Table 1).

**Table 1 T1:** Impact on the cardiovascular system.

Impact of TH on the cardiovascular system	Impact of the warming phase on the cardiovascular system
*Cerebral redistribution* • Reduced cerebral blood flow (CBF) • Preferential cerebral redistribution of left ventricular output (LVO) • TH causes vasoconstriction *Sinus bradycardia* • Slower repolarisation of the sinoatrial node Increased influence of the parasympathetic system LVO Reduction 60/70%	• Persistent cerebral redistribution • Preferential cerebral redistribution of the LVO • Decreased systemic vascular resistance (SVR) • Mobilisation (“exaggerated”) effect of inotropes • Increased HR • Increased cardiac output (CO)

## Objectives

2.

Haemodynamic changes were assessed by echocardiography doppler in neonates with HIE during TH and the warming phase.

### Primary objectives

2.1.

Assessment of left and right ventricular systolic-diastolic function during therapeutic hypothermia and in the warming phase.

### Secondary objectives

2.2.

•Assessment of cerebral circulation in neonates and controls by Doppler evaluation of blood flow in anterior cerebral artery (ACA) and middle cerebral artery (MCA), and flow in the superior vena cava (SVC) cardiac output (CO)•Assessment of visceral circulation in neonates and controls by Doppler blood flow evaluation in mesenteric artery (SMA).•Assessment of renal circulation in neonates and controls by Doppler blood flow evaluation in right renal artery (RRA).

## Methods and analysis

3.

### Study design

3.1.

This is a multicentre, prospective, case-control, observational study. The number of subjects under observation will be 100 neonates (study summery Tables 2, 3). The enrolment, intervention and assessment schedule is presented in Table 4. Initial echocardiography and cerebral and abdominal ultrasonography will be conducted according to physician recommendation on day 1/2 after birth—hypothermia group echo1 (T1) with repeat examination on conclusion of hypothermia, during warming i.e., on day 4/7 of life—hypothermia group echo2 (T2). In view of the need for cooling of the neonate from the first hour of life there is no possibility to conduct theses examinations prior to introducing hypothermia.

**Table 2 T2:** Study summary.

Title	Echocardiographic and Ultrasound Evaluation of Haemodynamic Parameters in Hypoxic Neonates Treated With Hypothermia.	
Methodology	Multi-centre, prospective, case-control, observational study.	
Study duration	The study will take place from June 2021—June 2023	
Study Centre(s)	Neonatal Clinic and Neonatal Intensive Care unit, Warsaw Medical University [name]	
	ŻELAZNA Medical Center Ltd St. Sophia's Specialist Hospital Medical Centre Department of Prematurity and Neonatal Pathology	
Objectives	**Primary objectives**:	
	Assessment of contraction-relaxation function of the left and right ventricle during therapeutic hypothermia and warming period.	
	**Secondary objectives:**	
	• Assessment of cerebral circulation in neonatal study and control subjects by doppler assessment of blood flow in the anterior cerebral artery (ACA) and medium cerebral artery (MCA), and flow through the superior vena cava cardiac output (SVC(CO))	
	• Assessment of visceral circulation in neonatal study and control subjects by doppler assessment of blood flow in the mesenteric artery (SMA)	
	• Assessment of renal circulation in neonatal study and control subjects by doppler assessment of blood flow in the right renal artery (RRA)	
Number of Subjects	100 neonates (50 subjects and 50 controls).	
Diagnosis and Main Inclusion Criteria	Inclusion criteria (subjects)	Exclusion criteria
	• Neonates aged ≥35 weeks of gestation with an episode of perinatal hypoxia	• Absence of parental or guardian consent for participation in the study
	• Neonates eligible for hypothermia treatment according to the Standa • ds of Medical Care for the Neonates in Poland (Table 5)	• Congenital cardiac abnormalities
		• Genetic abnormalities
		• SGA < 10 centiles
ClinicalTrials.gov ID:	NCT05574855	

**Table 3 T3:** Strong sides and limitations.

**What is known about the subject?**
• TH has a neuroprotective action in neonates with HIE
• Decrease in body temperature together with the negative consequences of episodes of HIE may exacerbate respiratory and circulatory failure
• Physiologically, the warming phase increases heart cardiac activity and increases systemic pressure, however, the precise impact on the cardiovascular system has not been studied. The haemodynamic instability during this phase requires further observation.
**What this study adds?**
• The haemodynamic changes in the circulatory system during TH and in the warming phase in comparison with the neonatal control group will be assessed.
• The impact of TH and the warming phase on the cardiovascular system including cerebral, visceral and renal circulation will be determined.
**Limitations**
• Cardiovascular haemodynamics during TH may also be disturbed by the administration of inotropic, anticonvulsant sedative agents as well as mechanical ventilation or thrombotic changes.
• The specificity of the transient circulation (presence of patent ductus arteriosus, patent foramen ovale) may interfere with some echocardiographic measurements, such as CO (Cardiac output) for LV (left ventricle) and RV (right ventricle).

**Table 4 T4:** Proposed schedule of enrolment.

Study plan	Birth	1–2 days	3–7 days	0–30 days*
Anthropometry	X			
Medical history collection	X			X
Enrolment	X			
Eligibility assessment		X		
Medication (inotropics, sedatives, anticonvulsants)				X
Ultrasound of brain				X
MRI brain				X
Echocardiography		X^1^	X^2^	

X^1^–1 echo for group T (T1), X^2^–2 echo for group T (T2) and echo in group *N* (*N*).

* Entire observation period.

Images and clips from examinations conducted for indications, other than hypothermia, most frequently because of difficult adaptation, will be used for neonates in the control group (*N*). The study will take place in the period June 2021–June 2023. The proposed protocol of the study is shown in Figure 1.

**Figure 1 F1:**
[figure not shown]
Proposed study protocol.

### Study population

3.3.

The study will include 100 neonates (50 subjects and 50 controls).
•Neonates with gestational age ≥35, who experienced an episode of perinatal ischaemia and who were qualified for hypothermia treatment according to the Standards of Medical care of Neonates in Poland will be enrolled to the subject group (T) (Table 5)•Healthy, term neonates, who underwent echocardiography on days 3–7 of life (after closure of ductus arteriosus, or with trace, insignificant haemodynamic ductus arteriosus) for reasons such as difficult adaptation, gestational diabetes of the mother etc.

**Table 5 T5:** Indications for hypothermic treatment according to the standards of medical care of neonates in Poland 2021 (3).

Indications for TH		
Criteria Group A. Neonates born at ≥35 weeks of gestation, who experienced a period of hypoxia and at at least one of the factors in each of the sub-groups		Group B-neurological criteria. Neonates fullfilling the criteria of group with A with fluctuating states of consciousness who has at least one of the following factors:
Sub-group 1	Sub-group 2	– Hypotonia – Abnormal response to stimuli, including abnormal occulomoor or pupillary reflexes – Absent or weak sucking reflex – Clinically confirmed convulsions
– Apgar score ≤5 week 1, 3, 5, 10 min after birth – Continuous resuscitation with tracheal or mask withinn 10 min after birth	– Cord blood or blood pH within 1 h of life ≤7, however, with specicif assesment of pH results in the region of 7.01–7.15 – A BE base deficiency of at least 16 mmol/l cord blood or other samoles samples within 60 min after birth.	

Enrolment of patients will be based on patient medical records. Physicians responsible for recruitment of patients will gather additional information associated with the inclusion and exclusion criteria (Table 6) through detailed history, taking into account the clinical condition of patients and the results of tests. The study procedure will be explained to patient's guardians who will also receive an information leaflet. Guardians will then be asked to provide two copies of informed consent. Consent forms and information papers will be provided solely in the Polish language.

**Table 6 T6:** Inclusion and exclusion criteria.

Inclusion criteria (subjects)	Exclusion criteria
• Neonates aged ≥35 weeks of gestation with an episode of perinatal hypoxia • Neonates eligible for hypothermia treatment according to the Standards of Medical Care for Neonates in Poland (Table 5)	• Absence of parental or guardian consent for participation in the study • Congenital heart defects • Genetic defect • SGA < 10 centiles

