### Strengths of the study

3.6.

To assess the hemodynamics of the circulatory system, the authors also used echocardiographic measurements, the value of which is independent of the presence of DA, PFO, HR, age, body weight, such as the TEI index for RV and LV, and used the tissue Doppler function to assess the myocardium.

An additional advantage of the study is the large size of the study group compared to other publications.

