## Study outcomes

5.

5.1.

•Assessment of the influence of TH on systolic-diastolic functions of the left and right ventricles in comparison with the control group•Assessment of the effect of the warming phase on the systolic-diastolic functions of the left and right ventricles in comparison with the control group

5.2.

•Assessment of the influence of TH on the cerebral, visceral and renal circulation in comparison with the control group•Assessment of the effect of the warming phase on the cerebral, visceral and renal circulation in comparison with the control group

This study assesses the hemodynamic changes by means of echocardiographic Doppler examination in neonates with HIE during TH in the warming phase in comparison with the control group of healthy neonates.

The intention is to assess the impact of TH on the cardiovascular system, including the cerebral, visceral and renal circulation.

TH may have an adverse effect on the cerebral circulation by increasing vascular resistance and loss of adaptation of the cerebral vessels, which in turn can lead to hypoperfusion of vital organs.

The effect of the warming phase on the cardiovascular system by increasing heart rate and improving cardiac output will also be carefully examined. The assumption is that the changes in blood pressure (systolic/diastolic) have a decisive impact on the metabolism of drugs, including vasopressors/inotropics, which in turn affects their choice and fluid therapy.

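### The influence-of-hypothermia outcomes compare cooled infants on day 1–2 with controls scanned once on days 3–7, so normal circulatory transition would be reported as an effect of hypothermia

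*Protocol article*

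**What the plan says.** All references are to the protocol article.

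- **Cooled group, first scan.** Section 3.1 says that the initial echocardiography and ultrasonography "will be conducted according to physician recommendation on day 1/2 after birth—hypothermia group echo1 (T1"). The second scan, T2, is taken during warming on day 4/7. The same section rules out any scan before cooling starts.
- **Controls.** Section 3.3 admits "Healthy, term neonates, who underwent echocardiography on days 3–7 of life (after closure of ductus arteriosus", or with a trace, haemodynamically insignificant duct. Table 4 agrees: its day 1–2 echo is marked for T1 only, and the single control echo sits in the day 3–7 column.
- **Outcomes.** Section 5.1 lists "Assessment of the influence of TH on systolic-diastolic functions of the left and right ventricles in comparison with the control group" and a matching item for the warming phase. Section 5.2 repeats the pair for cerebral, visceral and renal circulation. Section 5 does not label 5.1 as primary, but it matches the primary objective in 2.1: "Assessment of left and right ventricular systolic-diastolic function during therapeutic hypothermia and in the warming phase".
- **Acknowledged limits.** Table 3 concedes that "The specificity of the transient circulation (presence of patent ductus arteriosus, patent foramen ovale) may interfere with some echocardiographic measurements", with cardiac output as the example. It does not say that controls are scanned after that phase.
- **Claimed strength.** Section 3.6 says that the study also uses measures "the value of which is independent of the presence of DA, PFO, HR, age, body weight", such as the Tei index.

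**The concern.** The circulation changes over the first days of life whether or not an infant is cooled. If every cooled measurement comes from the first two days and every control measurement from later, after the duct has closed or become insignificant, the difference between groups contains that normal change. A study in which cooling had no cardiac effect could still find a difference, and section 5 would have it reported as the influence of TH. This touches the outcome that corresponds to the primary objective and the parallel organ-flow outcome. The sampling scheme fixes the problem: no control data are collected on day 1–2, so no later analysis can recover the missing comparison.

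**Working it through.** **Step 1: which scans can form each contrast**

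| Outcome (5.1 and 5.2) | Cooled-group scan | Control scan | Age overlap |
|---|---|---|---|
| Influence of TH | T1, day 1/2 | N, days 3–7, duct closed or insignificant | None |
| Effect of warming | T2, day 4/7 | N, days 3–7, duct closed or insignificant | Substantial |

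T1 is the only scan during cooling and N is the only control scan, so the first row is forced. The latest T1 day is 2 and the earliest control day is 3. An age term in a model for T1 v N would rest on extrapolation alone. Ductal state is a second systematic difference, since it is a condition for controls and not for the cooled group.

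**Step 2: what the age-independence claim covers**

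Section 3.5 lists 8 left-ventricular parameters (MPI by two methods, FS, LVO, S′, MAPSE, E:A, E′:A′) and 6 right-ventricular ones (MPI by two methods, S′, TAPSE, E:A, E′:A′), 14 in all. Four of them are MPI (Tei) measures. Section 3.6 gives the Tei index as an example and then mentions tissue Doppler. It makes no individual claim of age independence for FS, LVO, MAPSE, TAPSE, E:A or the organ-flow indices behind 5.2.

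**Step 3: how sensitive the test would be to an age-only shift**

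Section 9 gives the general noncentral F formula but no alpha, effect size, SD or number of levels. The planned 100 infants therefore cannot be reproduced from it, and the point does not depend on that number.

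Inputs: n = 50 per group (section 3.3). Assumed: two-sided alpha 0.05, k = 2 levels, true TH effect zero, and a shift of d SD between day 1–2 and days 3–7.

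- Noncentrality: λ = n Σ(μᵢ − μ̄)²/σ² = 50 × 2 × (d/2)² = 25d².
- Rejection probability: P(F(1, 98, λ) ≥ F₀.₉₅(1, 98)).

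| Assumed age shift d (SD) | λ = 25d² | Chance of a significant T1 v N difference |
|---|---|---|
| 0 | 0 | 0.05 |
| 0.2 | 1.00 | 0.17 |
| 0.3 | 2.25 | 0.32 |
| 0.5 | 6.25 | 0.70 |
| 0.8 | 16.00 | 0.98 |

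With k = 3 (T1, T2 and N treated as independent groups, only T1 shifted) the last four values are 0.16, 0.32, 0.73 and 0.99.

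**Step 4: precision if controls were divided between two windows**

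The detectable difference at 80% power is approximately (1.96 + 0.84) × √(1/n₁ + 1/n₂):

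- 50 v 50: 2.80 × √(1/50 + 1/50) = 0.56 SD; exact noncentral t, 0.57 SD.
- 50 v 25: 2.80 × √(1/50 + 1/25) = 0.69 SD; exact noncentral t, 0.70 SD.

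**The case against.** The best defence is that the control window looks partly deliberate. Section 3.3 ties it to ductal closure, and Table 3 explains that an open duct or foramen ovale disturbs some measurements. A stable circulation is a recognisable reference state. That stands as a reason for choosing the window, but it does not support reading T1 v N as the influence of TH.

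A second defence is section 3.6. If its claim is accepted, the Tei index is spared. A reader might go further and count exactly which of the 14 ventricular parameters are left exposed. The text does not allow that, because its list is introduced by way of example. What it supports is that no individual claim is made for the parameters named in step 2.

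Three other stronger readings are not supported:

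- **That the abstract contradicts section 3.3.** It says "In neonatal controls these examinations will be performed for indications other than hypothermia", which could suggest both time windows, but it gives no control days. It is ambiguous, and section 3.3 and Table 4 settle the matter.
- **That the T1-to-T2 change is a compromised outcome.** That change would run over 2 to 6 days of maturation (4 − 2 to 7 − 1) with no control change to subtract. But all four items in section 5 are comparisons with controls.
- **That an age-matched control would isolate TH.** The cooled infants also have HIE and, per Table 3, may receive inotropes, sedatives, anticonvulsants and ventilation. Matching on age leaves those differences in place.

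**Conclusion.** The point holds for the T1 v N contrast. The schedule and the outcome definitions together make group completely confounded with postnatal age, and controls are further selected on ductal state. Analysis cannot undo this. The conclusion rests on the stated scan days and needs no numerical assumption.

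The rejection rates of 17%, 32% and 70% for shifts of 0.2, 0.3 and 0.5 SD show sensitivity under an assumed alpha of 0.05 and 50 v 50. They do not estimate the bias in this study, because the documents give neither a shift nor an SD.

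A reader might infer that all the case-control outcomes fail. They do not: T2 v N is roughly age-aligned and this point leaves it intact, although HIE and co-treatment still separate those groups. The matter should be corrected before results are reported, because it decides what the outcome matching the primary objective can be said to show.

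**What to change.** **Necessary changes, to wording only**

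- In section 5, stop describing T1 v N as the influence of TH. Report it as a descriptive contrast confounded with postnatal age, ductal state, HIE and co-treatment.
- Add this to the limitations in Table 3.
- Limit age-aligned case-control inference to T2 v N.
- Make clear in the abstract that controls have one scan, on days 3–7, unless the optional window below is added.

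These changes need no new data. They cost the study its causal label for the cooling phase.

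**Optional addition, where the clips exist**

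Amend section 3.3 and Table 4 to add clinically indicated day 1–2 control clips as a separate window, N1, without a ductal condition, and compare T1 only with N1. The amendment should state four things:

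- N1 removes only the age and ductal part of the confounding, so T1 v N1 still does not earn the influence-of-TH label.
- Availability is not established, least of all for the cerebral, mesenteric and renal Doppler clips that 5.2 needs.
- Infants scanned that early for clinical reasons may be less healthy than the controls now defined.
- Precision falls if the 50 controls are divided. With 25 in a window, the detectable difference at 80% power rises from 0.57 to 0.70 SD.

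### The hypothermia-versus-control outcomes compare scans at non-overlapping ages, so postnatal transition and ductal state, like HIE itself, cannot be separated from hypothermia

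*Protocol article*

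**What the plan says.** Section 3.1 (Study design) schedules the first scan of the hypothermia group "on day 1/2 after birth—hypothermia group echo1 (T1") and the second "during warming i.e., on day 4/7 of life—hypothermia group echo2 (T2"). It adds that no scan before cooling is possible.

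Section 3.3 (Study population) defines controls as healthy term infants "who underwent echocardiography on days 3–7 of life (after closure of ductus arteriosus, or with trace, insignificant haemodynamic ductus arteriosus"). The scans are existing clinical examinations done for other reasons. Table 4 has T1 alone under 1–2 days. Its footnote for the 3–7 day column reads "2 echo for group T (T2) and echo in group" N, so T2 and the single control scan share that column.

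The first outcome in 5.1 is "Assessment of the influence of TH on systolic-diastolic functions of the left and right ventricles in comparison with the control group". The first in 5.2 is "Assessment of the influence of TH on the cerebral, visceral and renal circulation in comparison with the control group". The second outcome under each number makes the same comparison for the warming phase.

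Two other places bear on this. The limitations in Table 3 say of the transitional circulation that "presence of patent ductus arteriosus, patent foramen ovale) may interfere with some echocardiographic measurements", with cardiac output as the example. Section 3.6 (Strengths) says the authors also used measures that do not depend on the ductus, foramen ovale, heart rate, age or weight, and names the Tei index for both ventricles.

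**The concern.** A contrast described as the influence of TH should set infants during TH against a comparator that differs mainly in TH. Here the two sides also differ in postnatal age at scan, in ductal state (restricted in controls, unrestricted at T1) and in HIE. The first days of life are when the circulation changes, and the protocol treats that as relevant: it lists it as a limitation and requires a closed or insignificant ductus in controls. A difference between T1 and controls could therefore reflect transition, asphyxia, cooling or any mixture. If it is reported under the present outcome wording, it will be read as an effect of cooling. One of the two primary outcomes and one of the two secondary outcomes are affected.

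**Working it through.** **1. Which scans can answer the outcome.** The only scan during TH is T1, and the only control scan is N. The first outcomes in 5.1 and 5.2 therefore reduce to T1 versus N.

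**2. Scan-age windows, on Table 4's single scale for T1 and N and section 3.1's narrower window for T2.**

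| Contrast | Hypothermia group | Controls | Overlap | Ductal condition |
|---|---|---|---|---|
| T1 v N | days 1–2 | days 3–7 | none | controls only |
| T2 v N | days 4–7 | days 3–7 | days 4–7 | controls only |

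For T1 v N the age gap is at least 3 − 2 = 1 day and at most 7 − 1 = 6 days, always in the same direction. With no shared ages, a regression on day of life could separate age from group only by extrapolation. For T2 v N the windows share four of the controls' five days, so adjustment for age is feasible.

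For 5.2 this takes the organ Doppler to be recorded alongside the echocardiogram, as sections 3.1 and 3.4 describe. Table 4 shows brain ultrasound only against the whole 0–30 day period and gives no separate control day.

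**3. Which parameters section 3.6 could spare.** It names only the Tei index. Section 3.5 also lists FS, LVO, S′, MAPSE, TAPSE, E:A, E′:A′, AcT:RVET, SVC flow, RI and the half-peak deceleration time. No independence from age or the ductus is stated for these. The deceleration time is introduced in section 3.4.B to deal with bradycardia, which is a different matter.

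**4. Size, as an illustration.** The planned 50 + 50 = 100 cannot be reproduced, because section 9 gives no significance level, power, effect size or SD. Assume two-sided 5%, no true TH effect, and a shift of d SD between the two scan ages from transition alone.

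- Standard error of the standardised difference: √(1/50 + 1/50) = √0.04 = 0.20.
- Probability of a significant result: Φ(d/0.20 − 1.96) + Φ(−d/0.20 − 1.96).

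| Assumed shift d | d/0.20 | Normal | t, 98 df |
|---|---|---|---|
| 0 | 0 | 5% | 5% |
| 0.2 SD | 1.0 | 17.0% | 16.8% |
| 0.3 SD | 1.5 | 32.3% | 31.8% |
| 0.5 SD | 2.5 | 70.5% | 69.7% |

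For scale, the difference detectable with 80% power is (1.960 + 0.842) × 0.20 = 0.56 SD.

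**The case against.** The best defence has four parts.

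- **Disclosure and mitigation.** The authors name transitional circulation as a limitation and chose the Tei index partly to get round it. Section 3.5 lists that index first, as the global measure for both ventricles. Nothing in the documents refutes the independence claim. A reader might infer that the whole primary outcome is biased by construction. The documents do not support that: on their own terms the Tei index escapes the age and ductal part, though not the HIE part, and the limitation speaks of some measurements, not all.
- **Unknown size.** A reader might also infer that a T1–N difference must appear even if TH does nothing. No figure in the documents shows a shift, or its direction, for any parameter. The percentages above are rejection rates under an assumed shift and are not evidence that one exists.
- **Feasibility.** The study is non-interventional, its control scans are existing clips, and no scan before cooling is possible. A stable post-transition reference group is an understandable choice. This explains the design but does not make T1 v N a measure of TH.
- **Larger non-comparability.** Even controls scanned on day 1/2 would be healthy infants, so cooling and asphyxia would remain inseparable. This is right, and it is a further reason to drop the causal wording.

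The abstract could be read as giving controls scans at both times. Section 3.3 and Table 4 are specific, and give one scan on days 3–7.

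**Conclusion.** The point stands in a bounded form. As scheduled, the TH-versus-control outcomes in 5.1 and 5.2 rest on T1 versus N, where hypothermia is fully confounded with postnatal age, ductal state and HIE. This follows from the schedule alone and needs no assumption about size. No analysis of these scans can undo it, so it is not a detail that a statistical analysis plan could settle.

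The age and ductal part applies to the listed parameters other than the Tei index, if the claim in section 3.6 is accepted. The HIE part applies to all of them. The size of the bias is unknown; the range of about 17% to 70% false TH findings rests on an assumed shift of 0.2 to 0.5 SD, 50 infants per group and two-sided 5%.

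The warming contrast, T2 versus N, is roughly age-aligned and can carry inference, but as a comparison of HIE treated with TH, in warming, against healthy controls. It does not isolate warming.

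**What to change.** In section 5:

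1. Make T2 v N the inferential between-group contrast, adjusted for day of life at scan. Birth and examination dates are already collected (section 7). State that it compares infants with HIE treated with TH, in warming, with healthy controls.
2. Report T1 v N descriptively, without attributing differences to TH. The exception is where existing clinical day-1/2 clips of control infants can serve as an age-matched comparator. Section 3.3 would then have to admit them, including its ductal condition, and HIE would still be inseparable from cooling.
3. Report T1 to T2 as within-infant change over time. It spans the same early days, so it combines rewarming, recovery and postnatal transition and is not an effect of TH.
4. For flow measures, report T2 v N by recorded ductal state (already part of the examination in section 3.4.A) as a sensitivity analysis only. Ductal state at T2 is observed after HIE and cooling, so restricting on it may select less affected infants.
5. Extend the Table 3 limitation to age at scan.

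The cost is wording and analysis only, with no new scans. One advertised primary contrast becomes descriptive, and the ductal sensitivity analysis uses fewer infants.
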